**Step I - First cohort of practices** **(26 practices, 59 physicians)**			

Start:	April 2008	April 2009	July 2010

Completed as of April 2011:	26 practices, 59 physicians	26 practices, 59 physicians	26 practices, 59 physicians

Projected completion:	January 2010 (Complete)	January 2011 (Complete)	February 2011 (Complete)

**Step II - Second cohort of practices** **(30 practices, 79 physicians)**			

Start:	April 2009	April 2010	October 2011

Completed as of April 2011:	30 practices, 79 physicians	1 practice, 2 physicians	--

Projected completion:	March 2011 (Complete)	March 2012	September 2012

**Step III - Third cohort of practices** **(27 practices, 53 physicians)**			

Start:	January 2010	January 2011	July 2012

Completed as of April 2011:	13 practices, 25 physicians	--	--

Projected completion:	June 2011	June 2012	June 2013

### Study setting

The project is set in primary care practices in the Champlain Local Health Integration Network (LHIN) located in Eastern Ontario, Canada. The Champlain LHIN is a culturally diverse region with a population of 1.2 million people who have chronic disease burdens and patient health outcomes that are comparable to Ontario and the rest of Canada [33]. Excluding walk-in clinics, all models of primary care practices in the selected geographic areas of the Champlain LHIN are eligible to participate in this project, including solo practices, group practices, community health centers, and academic health center teaching practices.

The Champlain LHIN was first divided into nine geographic regions using Geographic Information System mapping technology [34] and then the regions were grouped together into strata by their location (*i.e*., west, central, and east) (Figure 3). Next, a computer-generated randomization assigned each region within each stratum into one of the three steps. Randomization at the regional level was done (a) to ensure that each step was comprised of one region from each stratum (east, central, and west), (b) to ensure that each region per stratum had the same probability of being in any given step and thus the same probability of beginning the intervention at any given time point, and (c) because practice-level randomization was logistically impractical for traveling between practices randomly scattered throughout this large health region (16,000 sq. km). Using provincial administrative data, practice-level (*i.e*., practice model type, rurality, average physician age, gender mix) and patient-level (*i.e*., age, sex, socioeconomic status, number of comorbidities) characteristics of practices that consented to take part in IDOCC will be compared across the nine regions and across the three steps to assess any nonandomness of the randomization process, as well as across all practices and patients in Ontario to assess provincial representativeness.

**Figure 3 F3:**
[figure not shown]
**Geographic breakdown of the Champlain LHIN**.

### Practice recruitment

Prior to the initiation of the recruitment process for each step, we developed an up-to-date list of the contact information of all physicians practicing in the geographic regions of interest using a variety of physician listings, such as The College of Physicians and Surgeons of Ontario website, the yellow pages, the provincial directory of group practices and through direct contact with the practices. Practice recruitment was carried out using a modified Dillman approach involving reminders and repeat mailings [35]. While no compensation was offered to practices for participation, a pre/post-intervention chart audit measuring the quality of their practice's overall cardiovascular care and the opportunity to obtain continuing professional development credits upon completion of the program (15 Mainpro-C credits, http://www.cfpc.ca/MainproCCredits/ acted as incentives. Practices were enlisted into the IDOCC program if at least one physician from that practice agreed to participate in the project. Practices agreeing to take part in the project were asked to fill out a practice-characteristic survey highlighting details about their practice, including number of patients for the physician, primary care model type, years in practice, etc. The consent signed by each physician allowed the project team to collect information from their patient medical charts and to link this information to the province's health administrative databases. Practices entered the project immediately after consenting to the project. We also completed nonparticipant surveys for the practices that decided not to take part in the project. The purpose of the survey is to identify reasons for not wanting to participate and collect data on practice characteristics so that we could assess participant selection bias.

### Target patient population for quality improvement

The aim of the IDOCC project is to improve the quality of care delivered to those patients with and at high risk of CVD. This includes patients being over 40 years of age with at least one of the following four criteria: (1) CVD including coronary artery disease, cerebrovascular disease (documented stroke and/or TIA), or peripheral vascular disease; (2) diabetes mellitus; (3) chronic kidney disease; and/or (4) be at high risk for CVD based on the presence of at least three of the following cardiovascular risk factors: age (males ≥ 45, females ≥ 55), smoker, hypertension, and dyslipidemia [36].

### Components of the IDOCC project

Key components of the IDOCC project include using the Outreach Facilitator to deliver elements of the chronic care model to each practice (the healthcare organization of interest). The practice outreach facilitation approach includes audit and feedback, consensus building, regular meetings (monthly to quarterly) with the practices, and interactive collaborative meetings:

a) Practice outreach facilitation: Four health professionals with master's degrees and clinical and managerial experience are employed as Practice Outreach Facilitators and work with 10-15 practices each. All had previous primary care experience and underwent a seven-week intensive training course focused on quality improvement and change-management techniques, the chronic care model, and system tools for cardiovascular care, including the evidence-based guideline used by the IDOCC project http://www.idocc.ca. This training provided them with the knowledge base and hands-on training required to effectively support healthcare providers in implementing changes to their practices.

i) Audit and feedback: The chart audits are completed by trained chart abstractors who randomly select 66 target-population patient charts per practice to assess the pre-intervention performance of each practice [37]. Information is collected regarding disease/risk factor screening, prescribing, community and self-management support referrals (*e.g*., referral to smoking cessation programs), and clinical outcomes for patient groups (*e.g*., blood pressure measures, hemoglobin A1c results). The Outreach Facilitator presents these chart audit results to all primary care providers and relevant office staff in the practice during a 30-60 minute meeting using a Microsoft PowerPoint (Microsoft Corporation, Redmond, WA, USA) presentation. The practice's performance is compared to the average performance across all IDOCC project participants and published regional numbers in order to highlight both areas of high-quality care and potential areas for improvement.

ii) Consensus building and regular meetings: The Outreach Facilitator then works with the primary care providers and relevant office staff to help them identify opportunities for improvement and select appropriate strategies to address these opportunities by incorporating a chronic care model approach. Goal setting, planning, and implementation are based on the Plan Do Study Act cycle, which is a common quality-improvement tool [38]. The Outreach Facilitators regularly meet with healthcare providers over the two-year intervention period to support practices in implementing system-level changes to achieve their goals. The Outreach Facilitator supports health providers in initiating, sustaining, and measuring changes to their practice but does not take the lead in implementing these changes. Members of the practice work towards the changes they selected under the guidance and support of the Outreach Facilitator. The support includes both aiding with implementing changes and helping practices determine roles for interested team members.

Outreach Facilitators regularly meet with practice members to support change implementation and to build a trusting relationship. Relationship building has been cited as an important aspect of the facilitation process and is based on continuity of contact and the personalities of the practices and the Outreach Facilitators. Physicians participating in a past facilitation study cited the necessity of Outreach Facilitators to be available, knowledgeable, and encouraging of new ideas and involving all practitioners [39].

iii) Interactive collaborative meetings: A series of cardiovascular-care-themed half-day collaborative meetings for IDOCC participants are being held in different locations within the region. These meetings are designed to be highly interactive, as they involve group brainstorming sessions, breakout group discussions, and participants sharing experiences and approaches implemented in their practices. Topics are determined based on requests from participating physicians and, to date, have included addressing challenges in engaging patients in self-management, connecting with local pharmacists and other community resources available to patients, and diabetes care. Closely linked to the meetings are knowledge translation newsletters, which highlight particular areas for quality improvement. Newsletter topics have included smoking cessation strategies, hypertension, self-management support, and diabetes care (see http://www.idocc.ca).

b) Chronic care model: The quality improvement approach is grounded in key elements of the chronic care model (Figure 1) in order to facilitate rapid knowledge translation and practice-level changes. Outreach Facilitators focused on the following four elements: (1) evidence-based decision support for providers, (2) delivery system redesign for practices, (3) enhanced self-management support tools provided to practices to help them engage patients, and (4) increased community resource linkages for practices to enhance referral of patients. We are not specifically focusing on clinical information systems, as the majority of the practices in our health region are still paper based. The Outreach Facilitator will, however, support development and optimization of clinical information systems when identified as a need by the practice.

i) Decision support: Decision support is guided primarily by the use of an integrated CVD care guideline: The Champlain Primary Care CVD Prevention and Management Guideline http://www.idocc.ca. The goal of the Guideline is to harmonize the management and target outcomes for multiple vascular conditions (coronary artery disease, TIA/stroke, diabetes, renal failure, and peripheral vascular disease), summarize evidence-based strategies for the detection and management of these vascular conditions and their associated risk factors (high blood pressure, high cholesterol, smoking, physical inactivity, and obesity), and maximize the use of local resources and tools in the provision of care. The Guideline is a very valuable tool, as most primary care physicians struggled to follow multiple, sometimes conflicting guidelines for each individual cardiovascular condition or risk factor [10,40]. The Champlain CVD Prevention and Management Guideline is the first Canadian guideline for primary care that includes standardized care pathways for patients with multiple chronic disease and cardiovascular risk factors. It was developed based on the recommendations of seven Evidence Monitoring Committees established for each of the seven risk factors targeted by the IDOCC project: hypertension, dyslipidemia, diabetes, chronic kidney disease, smoking, obesity, and physical inactivity [41].

Upon enrollment, all practices are provided with a paper copy of the Champlain CVD Guideline in binder format and directed to the IDOCC website http://www.idocc.ca for an annually updated online version of the Guideline. At the initiation of the intervention, each Facilitator provides an overview of the Guideline to each practice team, highlighting the development, organization, and strengths of the Guideline. In subsequent visits, the Facilitator commonly refers back to the Guideline in order to stress specific evidence-based practices or to point out clinical targets and community resources.

ii) Community resources: A key feature of the Champlain CVD Prevention and Management Guideline is the community resource section in which all programs relevant to cardiovascular care for a given condition or risk factor are listed. For example, current community smoking cessation programs and exercise programs are listed with referral information specific to each region--this information is kept up to date by both the work of the Facilitators and linkages established within the Champlain CVD Prevention Network. An annual update is done on the online version of the Guideline. In cases where practices require additional information from community resources, Facilitators act as liaisons, connecting directly with education and community programs.

iii) Self-management support: Many practices are interested in enhancing self-management support within their practices. Tailored plans that are practice specific are developed to support these practices using various approaches, such as incorporating goal setting and action planning into patient visits. The IDOCC project also developed an inventory of self-management support tools such as pocket cards, flow sheets, questionnaires, and patient self-management action plan forms to help physicians improve their delivery of evidence-based care. Tools can be accessed at http://www.idocc.ca/en_toolkits.php.

iv) Delivery system redesign: In helping physicians reach their goals, the Outreach Facilitators focus on assisting practices set up new systems and processes to help improve care delivery. Specific examples of improvement strategies include the utilization of registries to track patients with certain conditions, recall systems, reminder systems, and group visits for patients with common conditions (*e.g*., several diabetes patients come in at one time to have screening tests performed and to learn about self-management). These systems are implemented into practices using a tailored approach based on practice needs and available resources. For example, some practices have electronic medical records (EMRs) that allow them to filter their patient lists to create disease-specific registries and recall systems, while other practices that use paper charts create Microsoft Excel (Microsoft Corporation, Redmond, WA, USA) documents or cue cards to track their high-risk patients.

### Data collection

The primary source of data collection consists of repeated chart audits [42] of the same randomly selected patient population from each participating practice. Chart Abstractors visit practices on two separate occasions to collect chart data--once pre-intervention and once postintervention.

### Pre-intervention

Baseline data were required to provide each practice with feedback on their pre-intervention performance levels during the audit and feedback component of the intervention (Figure 2: Baseline-A).

### Post-intervention

After Year 2 of the intervention has ended in each practice, Chart Abstractors will return to collect medical chart data from both intervention years (*i.e*., Year 1: intensive phase, Year 2: sustainability phase) and to also collect pre-intervention baseline control data (Figure 2: Baseline-C). Participation in the follow-up data collection is encouraged through the following practices: (a) practices sign a consent form stating that they will allow a post-study follow-up, and (b) each practice is told that they will receive an end-of-study progress report highlighting changes in patient health and adherence to evidence-based guidelines.

Other data sources include Facilitator narrative reports, which are essentially field notes recorded after each practice encounter, including visits, email, and telephone encounters.

### Patient selection for medical chart abstraction

Patient medical charts are randomly selected using established chart-sampling protocols utilized by the project team in the past, including the "tape measure method" for paper and mixed charting systems (*i.e*., paper and electronic records) and a random number approach for electronic records [42].

Chart Abstractors are collecting cardiovascular-related diagnostic and screening data, clinical test results, drug prescription information, and notes regarding referrals to specialists or programs. All Chart Abstractors are blinded to the exact details of the intervention and are unaware of the details of the composite score that will be analyzed at the end of this study to reduce reporting bias.

This project, including its chart audit protocol, was approved by both the Ottawa Hospital Research Ethics Board and the Bruyère Continuing Care Research Ethics Board. In accordance with the Tri-Council Policy Statement, individual patient consent was not required, since (a) the project was targeted at changing physician practice behavior within established standards of care and project staff did not work directly with the patients, (b) IDOCC will examine and report only aggregate practice population data, and (c) this project posed minimal risk to the welfare and privacy of the patients [43].

### Quality control

To ensure the consistency and quality of the abstracted data across Chart Abstractors, a four-part quality-monitoring process was established, which includes (1) standardized protocol implementation, (2) extensive data abstraction training, (3) continuous re-abstraction and validation to monitor the interrater reliability between Abstractors, and (4) constant feedback and retraining. Our overall baseline interrater reliability kappa value was 0.91, and the overall percent agreement was 94.3% [37].

### Narrative reports

Practice Outreach Facilitators are completing a narrative summary in which they document facilitation activities for each practice encounter, including face-to-face visits, telephone calls, and emails. The narratives are structured based on the chronic care model and include both long-term and short-term goals and related activities. They also include details related to challenges and barriers to change within the practice. Investigators meet on a bimonthly basis to review a sample of the narratives to monitor data quality.

### Project outcomes

Composite scores are widely employed in cardiovascular interventions targeting multiple care processes as they not only reduce sample-size requirements but also provide an overall picture of interventional benefits and group performance [44]. For this reason, a quality of care (QOC) composite score was chosen as the primary outcome for this project.

The QOC composite score reflects practice adherence to recommended process-of-care maneuvers, as outlined in the Champlain CVD Prevention and Management Guideline. The maneuvers making up the composite score are listed in Table 3 and were collected through chart audits. The QOC composite score for this project is measured at the patient level and can be summarized by the following formula:

$$\begin{array}{l} \text{QOC composite score}=\\ \frac{\sum \text{ of recommended process}-\text{of}-\text{care indicators }\text{performed}\text{ on patient}}{\sum \text{ of recommended process}-\text{of}-\text{care indicators for which the patient was }\text{eligible}} \end{array}$$

**Table 3 T3:** List of quality-of-care indicators

Condition/risk factor	List of indicators
Coronary artery disease	➢ Blood pressure checked in past 12 months?
	➢ Fasting blood glucose taken in past 12 months?
	➢ Lipid profile taken in past 12 months?
	➢ Waist circumference measured in past 12 months?
	➢ If waist circumference is above limits (male > 88 cm, female > 102 cm), was referral to a dietician or an exercise program recommended or discussed?
	➢ Was a cardiovascular disease medication (*e.g*., beta-blocker, ACE inhibitor) recommended/discussed/prescribed in the past year?
	➢ Was aspirin recommended/discussed/prescribed in the past year?

Chronic kidney disease	➢ Albumin/creatinine ratio checked in past 12 months?
	➢ Blood pressure checked in past 12 months?
	➢ Lipid profile taken in past 12 months?
	➢ Estimated glomerular filtration rate taken in past 12 months?

Diabetes mellitus	➢ Blood pressure checked in past 12 months?
	➢ Lipid profile taken in past 12 months?
	➢ Was a glycemic control medication recommended/discussed/prescribed in past year?
	➢ Hemoglobin A1c taken twice in past year?
	➢ Waist circumference measured in past 12 months?
	➢ If waist circumference is above limits (male > 88 cm, female > 102 cm), was referral to a dietician or an exercise program recommended or discussed?

Peripheral vascular disease	➢ Blood pressure checked in past 12 months?
	➢ Fasting blood glucose taken in past 12 months?
	➢ Lipid profile taken in past 12 months?
	➢ Was a lipid-lowering medication recommended/discussed/prescribed in the past year?
	➢ Was an ACE inhibitor or angiotensin receptor blocker recommended/discussed/prescribed in the past year?
	➢ Was aspirin recommended/discussed/prescribed in the past year?
	➢ Waist circumference measured in past 12 months?
	➢ If waist circumference is above limits (male > 88 cm, female > 102 cm), was referral to a dietician or an exercise program recommended or discussed?

Stroke/transient ischemic attack	➢ Blood pressure checked in past 12 months?
	➢ Fasting blood glucose taken in past 12 months?
	➢ Lipid profile taken in past 12 months?
	➢ Was aspirin recommended/discussed/prescribed in the past year?

Dyslipidemia	➢ Lipid profile checked in past 12 months?
	➢ Was a lipid-control medication recommended/discussed/prescribed in the past year?
	➢ Waist circumference measured in past 12 months?
	➢ If waist circumference is above limits (male > 88 cm, female > 102 cm), was referral to a dietician or an exercise program recommended or discussed?

Hypertension	➢ Blood pressure checked at least three times in past year?
	➢ Was a blood pressure control medication (*e.g*., beta-blocker, ACE inhibitor) recommended/discussed prescribed in the past year?
	➢ Waist circumference measured in past 12 months?
	➢ If waist circumference is above limits (male > 88 cm, female > 102 cm), was referral to a dietician or an exercise program recommended or discussed?

Smoking	➢ Was smoking status checked in the past year?
	➢ If patient smokes, was there counselling or referral to a smoking cessation program?
	➢ Was a smoking cessation drug (e.g., Nicotine patch, Champix, etc) recommended/discussed/prescribed in the past year?

ACE: Angiotensin Converting Enzyme

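### Two item rules printed in Table 3 look faulty: the waist limit is lower for men than for women, and the cessation-drug item is not limited to smokers

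*Protocol article*

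**What the plan says.** Under Project outcomes, the primary outcome is a patient-level ratio: recommended process-of-care indicators performed, divided by those for which the patient was eligible. On what goes into it, the article says: "The maneuvers making up the composite score are listed in Table 3 and were collected through chart audits". The indicators reflect adherence to recommended care "as outlined in the Champlain CVD Prevention and Management Guideline"; that guideline is not reproduced.

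Two rules in Table 3 matter here.

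- **Waist and referral.** The item reads "If waist circumference is above limits (male > 88 cm, female > 102 cm), was referral to a dietician or an exercise program" and goes on to ask whether this was recommended or discussed. The same limits appear in the coronary artery disease, diabetes, peripheral vascular disease, dyslipidemia and hypertension blocks. No other part of the article gives a waist limit.
- **Smoking.** The block has three items. The first, "Was smoking status checked in the past year", applies to anyone. The second is conditional: "If patient smokes, was there counselling or referral to a smoking cessation program". The third has no condition: "Was a smoking cessation drug (e.g., Nicotine patch, Champix, etc) recommended/discussed/prescribed in the past year".

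**The concern.** Both rules help decide which items enter a patient's denominator, so they form part of the definition of the primary outcome. Table 3 is the only place in the article where eligibility for single items is spelled out.

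Men's waists are larger on average than women's, so a sex-specific limit would be expected to be higher for men. The printed order is the reverse. Five identical entries do not confirm it, because one transposed entry copied five times would look the same.

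In the smoking block, the authors wrote a condition where they wanted one, and the first item shows that the block heading does not itself restrict the items to smokers. Taken at face value, the drug item therefore applies to every patient assessed under that block, and non-smokers would be marked as not having received something they do not need.

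The article also promises, under Limitations, to report each component of the composite separately. A wrong rule would then distort those component results directly, as well as the composite.

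**Working it through.** **1. Waist rule: who would change.** Compare the printed limits with the same limits under exchanged labels.

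| Recorded waist | Man, as printed | Man, labels exchanged | Woman, as printed | Woman, labels exchanged |
|---|---|---|---|---|
| up to 88 cm | not eligible | not eligible | not eligible | not eligible |
| above 88, up to 102 cm | eligible | not eligible | not eligible | eligible |
| above 102 cm | eligible | eligible | eligible | eligible |

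Only the middle row changes, and in opposite directions for the two sexes. The article gives no waist distribution, so the share in that row has to be assumed. With normal distributions:

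- men, mean 98 (SD 12) to mean 106 (SD 14): 43% down to 29%;
- women, mean 90 (SD 13) to mean 102 (SD 16): 38% down to 31%.

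These are shares of patients with a recorded waist in the five affected blocks. They are not changes in the composite.

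**2. The plan's own sample size, as a base.** Inputs from Sample-size calculation: difference 8 points, SD 18, ICC 0.18, 66 charts per practice, two-sided 5%, 90% power.

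- Patients per step without clustering: 2 × [18 × (1.960 + 1.282) / 8]² = 106.4.
- Design effect: 1 + 65 × 0.18 = 12.7.
- Practices: 106.4 × 12.7 / 66 = 20.5, so 21. With 20% attrition, 21 / 0.8 = 26.25, so 27. Both agree with the article.
- Effective patients per step at 21 practices: 21 × 66 / 12.7 = 109.1. Power = Φ(8/18 × √(109.1/2) − 1.960) = Φ(0.444 × 7.387 − 1.960) = 90.7%.

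**3. Drug item: effect on a non-smoker's score.** If a patient has k other eligible items and the drug item is added and never met, the score is multiplied by k/(k+1). The article's own example patients have 4 and 8 eligible items. With an assumed score of 60%:

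- k = 4: 60% becomes 48.0%, and an 8-point effect becomes 6.4;
- k = 8: 60% becomes 53.3%, and an 8-point effect becomes 7.1.

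**4. Drug item: effect on power.** The factor k/(k+1) shrinks the SD of non-smokers' scores as well as their effect. Assume k = 6, 80% non-smokers, mean score 60%, and the ICC unchanged.

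- Non-smokers: effect 8 × 6/7 = 6.86; SD 18 × 6/7 = 15.43; mean 60 × 6/7 = 51.43.
- Average effect: 0.8 × 6.86 + 0.2 × 8 = 7.09, which is 11% below 8.
- Overall variance: 0.8 × 15.43² + 0.2 × 18² + 0.8 × 0.2 × (60 − 51.43)² = 190.4 + 64.8 + 11.8 = 267.0, so the SD is 16.34.
- Standardised effect: 7.09 / 16.34 = 0.434, against 0.444, a loss of about 2%.
- Power at 21 practices: Φ(0.434 × 7.387 − 1.960) = 89.3%.

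The same formulas with k from 4 to 8, 70 to 90% non-smokers and a mean score of 50 to 70% give power between about 86% and 90%.

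**The case against.** The strongest reply is that the article shows no scoring error. On smoking, the formula divides by items for which the patient was eligible, and Quantitative analysis says that the number of eligible items varies between patients. Non-smokers may therefore already be left out of the drug item, in which case nothing changes. On waist, the limits agree in all five places and nothing else in the article contradicts them. Calling them reversed rests on general knowledge of body size, and only the guideline could settle it. A misprint confined to the article is also possible. This part of the reply stands, and it means a reader should not infer that the wrong patients have been scored.

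Three further inferences also go beyond the documents.

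- **A large loss of power.** Shrinking the effect while holding the SD at 18 gives 77 to 86% power at 21 practices (70 to 90% non-smokers, 4 or 8 other items). That overstates the loss, because an unattainable item compresses the scores too. In addition, the SD and ICC came from the pilot, and the 8-point target from simulations on pilot data. If the pilot used the same items, any dilution is already in the planning figures.
- **A large shift in the composite from the waist rule.** The 29 to 43% figures count patients under assumed distributions. Men would gain an item and women would lose one, so the net change is not determined, and nothing here shows a smaller treatment effect.
- **Bias between steps.** The same rules apply to every step and period. Facilitation could raise waist measurement and so bring more patients under the referral rule in intervention periods, but that is conjecture.

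The reply does not remove the need for a check. The reported kappa of 0.91 measures agreement, and two abstractors using the same wrong limit would agree. The eligibility covariate adjusts for how many items count, not for whether they are the right ones.

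**Conclusion.** The point holds as a probable fault in two printed rules of the primary outcome. The waist limits are in an implausible order in all five places, and the drug item lacks a condition that its neighbour has. Which waist limits are correct cannot be decided from the article.

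If the labels are transposed, eligibility for the referral item is wrong for men and women in the five blocks with a recorded waist above 88 and up to 102 cm: roughly 30 to 40% of each sex, under assumed distributions. If non-smokers are counted for the drug item, a 60% score falls to between 48% and 53% for a patient with 4 to 8 other items. Power falls from about 91% to about 89% under the central assumptions of six other items, 80% non-smokers and a mean score of 60%.

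The likely consequences are misclassified item eligibility, distorted component results and, through the drug item, lower composite scores. The loss of power is small, and no bias between steps is demonstrated. The check is still needed before scoring, because these rules define the primary outcome.

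**What to change.** Before any chart is scored:

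1. Compare the sex-specific waist limits in Table 3, the abstraction form and the scoring program with the Champlain Guideline, and correct whichever is misprinted. If Table 3 is wrong, all five entries change.
2. Derive eligibility for the referral item from the recorded waist and sex wherever the waist value was abstracted.
3. Limit the cessation-drug item to smokers, with the same condition as the counselling item, in both the table and the scoring program.
4. If charts have already been scored under a rule that proves wrong, rescore them and state the change when the composite and its components are reported.

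The cost is a correction to one table and a check of the scoring program. No new data are needed if waist values and smoking status were abstracted. The article says that clinical test results were collected but does not state that the waist measurement itself was recorded. Where it was not, the misclassification cannot be repaired without going back to the charts, and this should be reported.
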